| **S/No** | **Parameter** | **µ_o_** | **Δ** | **δ^2^** | **Desired % change in mean after 3 months** | **µ_a_** | **DE** | **Non response (20%)** | **N** |
| --- | --- | --- | --- | --- | --- | --- | --- | --- | --- |
| 1 | BMI(Kg/m^2^) | 22.9 | 4.6 | 21.2 | 5 | 21.8 | 1.5 | 0.8 | 204 |
| 2 | TC(mmol/L) | 4.6 | 0.78 | 0.6 | 5 | 4.4 | 1.5 | 0.8 | 178 |
| 3 | TG(mmol/L)* | 1.7 | 1.1 | 1.2 | 12 | 1.5 | 1.5 | 0.8 | 353 |
| 4 | SBP (mmHg) | 129 | 21.3 | 453.7 | 5 | 122.2 | 1.5 | 0.8 | 129 |
| 5 | DBP (mmHg) | 80.3 | 12.2 | 148.8 | 5 | 76.3 | 1.5 | 0.8 | 109 |
| 6 | FBG(mmol/L) | 4.8 | 1.6 | 2.6 | 10 | 4.3 | 1.5 | 0.8 | 120 |
| 7 | WHR (none) | 0.82 | 0.2 | 0.0 | 5 | 0.779 | 1.5 | 0.8 | 278 |

***Source:*** (14)

2.5 Sampling procedures: This study will also apply a multistage cluster sampling whereby; three out of five districts have been selected randomly from Dar es Salaam region. Thereafter, mapping of market places (clusters) will be done and in each selected district two market places will be randomly selected then randomized one to receive an intervention package (health education and plate model) and another to receive a placebo (health education) . The step will be followed by mapping of food vendors to identify eligible food vendors and form a sampling frame per each cluster. Thereafter, probability proportion to size will be done to determine the number of vendors to be recruited per each cluster. Food vendors will be also selected randomly from each cluster to participate in the study. Each selected food vendor will identify regular customers then consent to participate in the trial will be sought from all identified clients (**Table 2**).

Table 2 Summary for sampling procedure

| **Stage** | **Ilala** | **Ubungo** | **Kinondoni** |
| --- | --- | --- | --- |
| 1. Identify the market places(MP)/clusters | 5 | 9 | 8 |
| 2. Identify and match eligible MPs | 5 | 9 | 8 |
| 3. Select randomly the required number of MPs for the study | 2 | 2 | 2 |
| 4. Assign MPs randomly into control and intervention arms | 2 | 2 | 2 |
| 5. Mapping Food vendors(FVs) | xx | Xx | Xx |
| 6. Identify eligible FVs | xx | Xx | Xx |
| 7. Use probability proportion to size (PPS) to allocate ≥50 FVs | xx | Xx | Xx |
| 8. Mapping of eligible* regular clients per FV | xx | Xx | Xx |
| 9. Seek consent and recruits all regular clients /FV | xx | Xx | Xx |

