2.6 Material and method for each specific objective: A tool for data collection have been adopted from WHO STEP Survey questionnaire and other studies on similar topic(14,45–51). This tool will be then translated from English to Swhaili version. A tool also will consist of information including socio-demographic, behavioural, physical measurements and biological tests. A total of three focus group discussion (FGDs) involving street food vendors and six in-depth interviews with key stake holders will be conducted to assess their level of knowledge on type2 diabetes and hypertension risk factors and factors associated with adoption of food plate model and education package. Eight in-depth interviews will be conducted among public staff responsible with setting enabling and regulating working environment of food vendors. A three days training will be made to research assistants, this will involves orienting them on the study protocol, data collection tools and study ethics. **Table 3** shows the inclusion and exclusion criteria.

Table 3 Inclusion and exclusion criteria

| **Type of respondent** | **Inclusion** | **Exclusion** |
| --- | --- | --- |
| Street Food consumers | 1. Consuming at least three lunches meals/week to the same street food vendor (SFV) 2. Willing to participate in the study 3. Will remain in the study area for the duration of at least six months 4. Aged 25-64 years | Pregnant or lactating mothers |
| Street food vendors | 1. Vending food in the current site for not less than 6 months 2. Has at least 10 clients who have been consuming a least three lunch meals per week for not less than three months 3. Ready to implement the components required for an intervention model 4. Will remain vending food at same site for not less than six months 5. Aged 18 and above years | Not providing services daily |

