2.7.2 Plate Model: Before implementing the food plate model the consumers and vendors who will consent to be recruited for the intervention arm will be educated on how to prepare the standard and recommended food plate model and its hypothesized role of reducing metabolic risk factors of T2DM. We envisaged that knowledge about the current topic will influence practice and increase uptake of an intervention. The benefits of serving the food plate model will be explained to the vendors and these benefits will include serving small amount of carbohydrate, getting extra business by selling separate portion of vegetables and fruits after the project implementation thus getting more profit. For the consumers the benefits of plate model will include paying reduced price for carbohydrate since amount to be served will be the quarter of the normal served amount. Other advantages will include preventing the consumers from excess weight gain and contributing to balancing lipid T2DM metabolic risk factors. More emphasize will be given to the participants regarding the recommended ratio of fruits, vegetables, fats/protein and carbohydrate. Participants will be also instructed on how to ensure that the food plate model contain the recommended amount of potassium, magnesium and calcium levels. The food plate model will consists of more fruits and vegetables which will be half normal eaten plate before the intervention and each quarter will comprise carbohydrate and fats/protein. The participants will be insisted to avoid diary with high saturated fats and cholesterol.

2.8 Project monitoring: To ensure sustainability of the outcomes; the project will involve municipals officers during the implementation of the study so that they take lead in promoting supply and consumption of healthy diet. Intervention program will take three months(57). Monitoring will be done to ensure adherence and compliance as per study protocol requirements. This will involve signing a daily healthy plate form and weekly visits (intervention arm) while a daily lunch form and weekly visit (control arm). The main targets indicators will include mean of metabolic components (systolic and diastolic blood pressure, fasting blood glucose, body mass index, waist circumference, triglycerides and high density lipoprotein), proportion of respondents with high knowledge and positive attitude before and after intervention.

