2.9 Controlling bias and confounders: This project is prone to bias since food vendors will be responsible in identifying their regular customers a situation which is associated with selection bias, however, the vendors will be told that all identified clients will be approached to consent for the study. Interview bias which is associated with incomplete and inaccuracy data; this effect will be minimized by training data collectors and field supervision(58–62). This study is also prone to known and unknown confounders. Clusters randomization (market place), probability proportional to size allocation of vendors and multivariable analysis approaches will minimize confounding effects (58–62)**.**

2.10 Expected outcomes: The magnitude of type2 diabetes and its risk factors among consumers of urban street cooked food will be known. The level of knowledge and attitude on type2 diabetes and its risk factors among consumers and vendors of urban street cooked food will be known. Through this study the effects of health intervention (Health education and healthy eating plate model) on prevalence of metabolic risk factors of type 2 diabetes will be known. A model for monitoring and predicting metabolic risk factors of type 2 diabetes among consumers of urban street cooked food will be developed from this study. Consequently, the study findings will help to enhance and enrich the policy and guidelines for food regulatory authorities in Tanzania and elsewhere. Ultimately, the research findings will inform food policy and food related guidelines and will also help to improve food system in urban areas.

Table 5 Timeline and Milestones

| **Activity** | **Oct 2017-**  **Sept 2018** | | | | **Oct 2018-**  **Sept 2019** | | | | **Oct 2019-**  **Sept 20120** | | | |
| --- | --- | --- | --- | --- | --- | --- | --- | --- | --- | --- | --- | --- |
|  | **Q1** | **Q2** | **Q3** | **Q4** | **Q1** | **Q2** | **Q3** | **Q4** | **Q1** | **Q2** | **Q3** | **Q4** |
| 1. Writing proposal |  |  |  |  |  |  |  |  |  |  |  |  |
| 2.Application of Ethical Approval |  |  |  |  |  |  |  |  |  |  |  |  |
| 3. Attend monthly or quarterly supervisory meetings |  |  |  |  |  |  |  |  |  |  |  |  |
| 4.Attend at least 4 short courses & 5 conferences |  |  |  |  |  |  |  |  |  |  |  |  |
| 5.Write small proposals to mobilize l funds |  |  |  |  |  |  |  |  |  |  |  |  |
| 6. Write systematic review /meta analysis |  |  |  |  |  |  |  |  |  |  |  |  |

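### Markets are assigned to arms before vendors and clients are identified and consented, with no concealment described, so recruitment may differ between arms

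*Protocol*

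**What the plan says.** Section 2.5 selects two markets in each of three districts and randomises one to the package and one to health education alone. It then continues: "The step will be followed by mapping of food vendors to identify eligible food vendors and form a sampling frame per each cluster". Table 2 gives the same order:

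- Stage 4: "Assign MPs randomly into control and intervention arms".
- Stages 5 to 7: map vendors, identify the eligible ones, allocate at least 50 by probability proportional to size. The text adds: "Food vendors will be also selected randomly from each cluster to participate in the study".
- Stages 8 and 9: map regular clients per vendor, then "Seek consent and recruits all regular clients /FV". The text says: "Each selected food vendor will identify regular customers then consent to participate in the trial will be sought from all identified clients".

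Vendor eligibility in Table 3 includes "Ready to implement the components required for an intervention model".

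Three places bear on whether the arm is known at recruitment. Section 2.3 says that participants at intervention sites are not blinded. Section 2.7.2 says that "the consumers and vendors who will consent to be recruited for the intervention arm will be educated". Section A of the questionnaire in Appendix B records intervention or control at item 3 and consent at item 6.

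Section 2.9 accepts that naming of clients by vendors is a source of selection bias. Its specific safeguard is that "the vendors will be told that all identified clients will be approached to consent for the study". It also relies on cluster randomisation, proportional allocation of vendors and multivariable analysis.

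**The concern.** Randomising markets makes the arms comparable in expectation only if the people who enter from each market do not depend on its arm. Here every individual enters after the arm is fixed. If vendors, recruiters or clients know the arm, there are three routes by which the samples could come to differ:

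- **Vendor eligibility.** Readiness to implement the package is judged after assignment. In a plate market it can screen out reluctant vendors. In a control market a vendor can declare readiness without having to act on it.
- **Naming of clients.** Vendors name their own regular clients, and the Operational definitions mark the definition of a regular client as still to be settled.
- **Consent.** Section 2.7.2 attaches plate-specific advantages, such as a lower price for the carbohydrate portion and extra business for vendors. These give people reasons to join that depend on the arm.

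At stake is the between-arm comparison of the metabolic outcomes. A difference created by recruitment does not shrink as more people are enrolled, and no later analysis can recover clients who were never named or who refused.

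**Working it through.** **Order and safeguards, set side by side**

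- *Random choice of vendors (2.5)* draws from the eligible list, which is made after assignment and includes the readiness criterion. It does not protect the list itself.
- *Approaching all named clients (2.9)* limits selection after naming. It does not control whom a vendor names or who agrees.
- *Cluster randomisation and proportional allocation (2.9)* act on markets and on numbers of vendors, not on who enters.
- *Baseline data from both arms (2.3), the pre-post mixed model (2.6.4) and multivariable analysis (2.9)* can reduce a measured imbalance. They cannot reach unmeasured differences such as motivation.
- *The endline comparison (2.6.4)* is an independent t-test, which makes no adjustment for baseline.

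**The plan's own figure**

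Inputs from Table 1 for waist-hip ratio: mean 0.82, SD 0.2, target 0.779, design effect 1.5, division by 0.8 for 20% non-response, N = 278. Alpha and power are named without values. One-sided 5% and 80% are assumed here because they reproduce the figure with the one-sample formula:

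- n = [0.2 × (1.645 + 0.842) / 0.041]² ≈ 147.1, rounded up to 148.
- 148 × 1.5 / 0.8 = 277.5, which gives 278 per arm and 556 in total.

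The figure reproduces, and the present point does not change it. It supplies the yardstick: a target difference of 0.041, or 0.041 / 0.2 = 0.205 SD.

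**Illustration of size (assumed values, not in the documents)**

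Suppose a share f of one arm's clients differs by g SD because of arm-aware naming or consent. The arms then differ by f × g SD with no treatment effect. The false-positive rate below is for a two-sided 5% test of unadjusted endline means by normal approximation, with standard error √(2 × 1.5 / n) in SD units.

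| f | g (SD) | Shift (SD) | Shift in ratio | Share of target | False positives, n = 278 per arm | False positives, n = 222 per arm |
| --- | --- | --- | --- | --- | --- | --- |
| – | – | 0 | 0 | 0% | 5.0% | 5.0% |
| 10% | 0.5 | 0.05 | 0.01 | 24% | 7.7% | 7.1% |
| 20% | 0.5 | 0.10 | 0.02 | 49% | 16.1% | 13.8% |
| 20% | 1.0 | 0.20 | 0.04 | 98% | 48.6% | 40.5% |

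The share of target is the shift divided by 0.205 SD; for example 0.05 / 0.205 = 24%. The 222 is 278 × 0.8. For a given shift the false-positive rate is higher with 278 than with 222 per arm, so a larger trial does not cure the problem.

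**The case against.** The order of steps is not in dispute, but several stronger readings are tempting and the documents do not support them.

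- **That the plan states the arm is known at recruitment.** It does not. Section 2.3 does not say when participants learn the arm or what control sites are told. The wording in 2.7.2 is loose, and item order on a form is weak evidence. The consent forms were not in the text reviewed, so a common consent text may already exist. Arm knowledge remains an inference, though a reasonable one, because three places point the same way and none describes concealment.
- **That section 2.9 concedes this bias.** It concedes selection bias from vendor naming. It says nothing about a difference between arms.
- **That the bias would favour the package.** Health-minded clients might join in plate markets, but so might heavier or more worried ones. The direction is unknown.
- **That vendors have wide discretion.** Table 3 sets countable criteria for clients, and stage 9 aims at all regular clients. With 556 / 50 = about 11 clients per vendor and a minimum of 10 regular clients for eligibility, a vendor near the minimum has little room to choose. Vendors with longer lists have more room, and differential consent remains possible in either case.
- **That readiness is required in one arm only.** Table 3 lists it for all vendors. Only its timing is open to criticism.
- **That 24% to 49% estimates the bias.** The gap behind those figures is assumed, and they apply to the unadjusted t-test. A measured baseline gap in waist-hip ratio is what the mixed model could address.

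These limits affect how firmly the point is put. They leave the sequence, the absence of described concealment and the unmeasured differences untouched.

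**Conclusion.** The plan fixes a recruitment order that leaves the comparison open to differential recruitment, and its stated safeguards cover only part of the risk. That the sequence is as described is certain. That the arm is known when vendors name clients and clients consent is probable, but inferred.

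Size and direction cannot be estimated from the documents. The tabulated figures show only that modest assumed shifts of 0.05 to 0.10 SD would matter beside a target of 0.205 SD. They assume the Table 1 SD, the design effect of 1.5 and no baseline adjustment.

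A reader might infer that randomisation has been undone. The documents support a risk, not that conclusion. It is still worth removing before recruitment, because the order of recruitment is fixed by the protocol and not by the analysis, and the change is mainly one of sequence.

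**What to change.** In Table 2 and section 2.5, move stage 4 after stage 9. In both selected markets of a district:

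1. Map vendors and apply all eligibility criteria, including readiness to implement, in the same way.
2. Select vendors and list their regular clients.
3. Obtain consent with one common text and complete baseline.
4. Only then draw and disclose the assignment for that district.

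Item 3 of the questionnaire, the arm code, would be filled in afterwards. The wording on consent in 2.7.2 should be brought into line.

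If this is not feasible, at least list vendors and clients before assignment, and have recruiters who do not know the arm use one consent text in both markets.

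In either case, report the numbers listed, approached and consenting by arm.

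**Cost.** Baseline already precedes the intervention in both arms and the vendor and client counts in Table 2 are still blank, so the change is mostly one of order and consent wording. It does constrain scheduling: baseline, including the next-day fasting samples in 2.6.1, must finish in both markets of a district before either can start. Some vendors may withdraw on learning their arm, but such withdrawals can be counted and reported, whereas hidden selection cannot.

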2.6.1 Magnitude of type2 diabetes, behaviourial and its risk factors: The prevalence of type 2 diabetes among urban street cooked food consumers will be determined. A person will be considered to have diabetes if the reading for fasting blood glucose measured using Accu-check machine is >7.0mmol/L or is on medication for raised blood glucose. This study will also assess the prevalence metabolic and behavioural risk factors of type 2 diabetes. Prevalence of metabolic risk factors will be assessed as follow: being overweight or obese (BIM≥25Kg/M^2^), raised TC (≥5.1mmol/L), raised TG (≥2 mmol/L), low HDL (<1.03 mmol/l for Male and < 1.29 for Female), raised LDL (>2.6 mmol/L), Abnormal Waist Hips Ratio for male and female if the value is >0.8 and >0.9 respectively, raised Systolic BP (≥140mmHg) and Diastolic BP (≥90 mmHg) (17,18). Behaviorial assessement will including participating in physical activities as per recommended standard (≥600MET/week), Behaviourial assessment will include consumption of fruits and vegetables as per standard (≥5 days per week), non-harmful drinking (5 or less for male and 4 or less for female units of alcohol per week) and not consuming table salt will be assessed (18,52).

**Blood Pressure (BP) Measurements**: Blood pressure will be measured while patients are in a sitting position, using an M4 Omron® device. An average of the last two readings taken three times consistently after three minutes from the left arm will be treated as final reading and will be used during analysis(18). The final will be classified as raised blood pressure if BP of ≥140/90mmHg.

**Weight Measurement**: SECA® weighing scale will be used to measure weight. Participant will be asked to remove any heavy clothing (such as coats and shoes) and stand still on the weighing scale, with hands by their sides.

**Height Measurement:** Height will be measured with a SECA® stadiometer, while a patient is facing directly ahead. Patients will be instructed to remove their shoes, caps or head scarf, keep their feet together, and stand with their arms by the sides. Measurement will be taken with heels, buttocks and upper back in contact with the stadiometer.

**Body Mass Index (BMI):** The product of weight (in Kilograms) divided by height squared (m^2^) will give BMI. Categorization BMI will be as follows ; obesity is ≥30 kg/m2; Overweight if the BMI is > 25 but < 30kg/m2, and normal if the BMI is between 18-25kg/m2 and underweight if below 19 kg/m^2^ (53).

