| 7.Site preparation |  |  |  |  |  |  |  |  |  |  |  |  |
| 8.Finalize protocol |  |  |  |  |  |  |  |  |  |  |  |  |
| 9.Supervisory and Mentorship |  |  |  |  |  |  |  |  |  |  |  |  |
| 10.Baseline data collection |  |  |  |  |  |  |  |  |  |  |  |  |
| 11.Implement intervention package |  |  |  |  |  |  |  |  |  |  |  |  |
| 12.Data management and analysis for baseline |  |  |  |  |  |  |  |  |  |  |  |  |
| 13.Defend Thesis |  |  |  |  |  |  |  |  |  |  |  |  |
| 14. End line data collection |  |  |  |  |  |  |  |  |  |  |  |  |

2.11 Ethical consideration: An ethical clearance will be sought from the Medical Research Coordination Committee of the National Institute for Medical Research. Regional and district authorities will be informed about the aim and procedures of the study. During the study, participants will be informed about the aims and benefits of the study and a written informed consent will be obtained from each participant. Names will not be used and confidentiality will be maintained by keeping data collection questionnaire locked in a secure cabinet, while the electronic data file will be kept in a password protected computer. Participants who will be examined and identified with hypertension, or diabetes (high blood sugar) will be referred to the nearest health facilities for further management. Those who will be screened and found with abnormal cholesterol and body mass index will be counselled and advised on proper approaches for risk prevention and control. This protocol will be registered in order to comply with WHO’s  [Helsinki](http://www.wma.net/en/30publications/10policies/b3/index.html) Declaration which states that "Every clinical trial must be registered in a publicly accessible database before recruitment of the first subject".

Table 6 Budget for the study project

| **S/No** | **Item** | **Description** | **Year1 (Euros)** | **Year2 (Euros)** | **Year3 (Euros)** | **Total (Euros)** | **Source** |
| --- | --- | --- | --- | --- | --- | --- | --- |
| 1 | Salary/Stipend | 36 months | 4,560 | 4,560 | 4,560 | **13,680** | ASPIRE |
| 2 | Tuition Fees |  | 5,200 | 5,121 | 5,120 | **15,442** | ASPIRE |
| 3 | Training / Workshop | Pm | - | - | - | **-** | Vliruos/others |
| 4 | Supervision | Lump sum | 381 | 381 | - | **762** | ASPIRE |
| 5 | Research cost (lab) | Lump sum | 19,650 | - | - | **19,650** | ASPIRE/others |
| 6 | Equipment(lab) | Lump sum | 762 | - | - | **762** | ASPIRE/others |

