**Section E7: Step 1: Familial –Diabetes**

| **Q-Number** | **Question** | **Response** | **Code** |
| --- | --- | --- | --- |
| 102. | Have you ever had your blood sugar measured by a doctor or other health worker? 1. Yes 2. No |  | Qn102 |
| 103. | Have you ever been told by a doctor or other health worker that you have raised blood sugar or diabetes? 1. Yes 2. No |  | Qn103 |
| 104. | Have you been told in the past 12 months? 1. Yes 2. No |  | Qn104 |

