**Sehemu E7: Step 1: Historia ya Kisukari**

| 102. | Umewahi kupimwa kiwango cha sukari katika damu?  1. Ndiyo 2. Hapana |  | Qn102 |
| --- | --- | --- | --- |
| 103. | Katika miezi 12 iliyopita, umewahi kuambiwa na daktari au mtaalamu mwingine wa afya kuwa una ugonjwa wa kisukari?  1.Ndiyo 2. Hapana |  | Qn103 |
| 104. | Je umeambiwa hivyo ndani ya miezi 12?  1.Ndiyo 2. Hapana |  | Qn104 |

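### Consumers who already have diabetes stay in the fasting-glucose comparison and the Table 4 glucose model with no diabetes or medication term, and the Swahili form can miss known cases

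*Protocol*

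**What the plan says.** **Eligibility.** The only consumer exclusion in Table 3 (section 2.6) is "Pregnant or lactating mothers". No inclusion criterion concerns glucose, diabetes or its medication, and the last step of Table 2 is "Seek consent and recruits all regular clients /FV".

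**Diabetes is expected among those enrolled.** Section 2.6.1 counts a consumer as having diabetes if the reading "is >7.0mmol/L or is on medication for raised blood glucose". Section 2.11 adds: "Participants who will be examined and identified with hypertension, or diabetes (high blood sugar) will be referred to the nearest health facilities". It makes no distinction by arm.

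**Use of FBG.** Section 2.6.4 compares every metabolic risk factor between arms by t-test after the intervention. It adds a generalized linear mixed model (GLMM) for pre-post analysis. Its named list of primary outcomes does not contain FBG. Section 2.8 does name it: "The main targets indicators will include mean of metabolic components (systolic and diastolic blood pressure, fasting blood glucose". FBG also has a row in Table 1 and is a dependent variable in Table 4, whose covariates include neither diabetes status nor glucose medication.

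**Questionnaire (Appendix B).** English Qn103 asks "Have you ever been told by a doctor or other health worker that you have raised blood sugar or diabetes". Swahili Qn103 asks "Katika miezi 12 iliyopita, umewahi kuambiwa na daktari au mtaalamu mwingine wa afya kuwa una ugonjwa wa kisukari", which limits the question to the past 12 months. Qn122 asks about glucose medication on the day of the test only.

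**The concern.** Section 1.2 gives the purpose as lowering the chance of developing type 2 diabetes. In someone who already has it, FBG marks the disease and its control. A Table 4 model that pools these people with the rest mixes predictors of a risk factor with predictors of diagnosed or treated disease.

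Referral follows the baseline measurements, so any treatment it starts falls within the three months of follow-up. The endline FBG of these participants can then move for reasons unrelated to the plate. A small group with high, changeable values can also supply a large part of the variance against which the plate's effect is judged. FBG is the only glucose measure collected, so no other result could settle a doubtful one.

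**Working it through.** **1. The plan's own FBG figure.** Table 1 gives mean 4.8, SD 1.6, target 4.3, design effect 1.5, response 0.8 and N = 120. The protocol gives no values for alpha or power. One-sided 5% and 80% in a one-sample formula reproduce the row:

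(1.6 × (1.645 + 0.842) / 0.5)² = 63.3, rounded up to 64; 64 × 1.5 / 0.8 = 120.

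The SD of 1.6 comes from the cited population survey. If that survey included people with diabetes, the planned N already carries their variance, so no arithmetic error is claimed.

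**2. How many people.** Section 1.0 cites 9.1% for Tanzania in 2012. Applied here (assumption): 0.091 × 278 = 25 per arm, 51 of 556 in all.

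**3. Share of the FBG variance.**

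- Normal model with Table 1's mean and SD: t = (7.0 − 4.8) / 1.6 = 1.375. The proportion above 7.0 is 8.5%. Its share of the sum of squares is t·φ(t) + 1 − Φ(t) = 0.213 + 0.085 = 0.30. The between-group share agrees: with means 7.73 above and 4.53 below 7.0, 0.0846 × 0.9154 × 3.20² / 2.56 = 0.31.
- Two-group model with prevalence p = 0.091 and overall mean held at 4.8: share = p(1 − p)(m_d − m_n)² / 2.56, where m_n = (4.8 − p·m_d) / (1 − p).

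| Assumed diabetic mean m_d | m_n | Share of variance | SD left |
|---|---|---|---|
| 7.0 | 4.58 | 19% | 1.44 |
| 8.0 | 4.48 | 40% | 1.24 |
| 9.0 | 4.38 | 69% | 0.89 |

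The normal model puts as many people below 2.6 as above 7.0, which suggests that the real spread lies more in the right tail and that 30% may be low. Treated cases below 7.0 pull the other way.

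**4. Effect of referral.** If treatment lowers FBG by 1 to 3 mmol/L (assumption) in everyone with diabetes, an arm mean moves by 0.091 × 1 = 0.09 to 0.091 × 3 = 0.27. Within-arm change carries this in full. With equal uptake and prevalence it cancels between arms. A 20-point uptake gap (assumption) leaves 0.091 × 0.20 × 1 = 0.02 to 0.091 × 0.20 × 3 = 0.05 mmol/L, or 4% to 11% of the 0.5 target.

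**5. Would leaving them out sharpen the result?** Design effect 1.5 with 278 / 3 = 93 people per market puts about 34% of the arm-mean variance between markets. Hold that part fixed (assumption) and scale the remaining 66% by the variance ratio divided by the fraction of people kept:

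- truncated normal (SD 1.37): √(0.66 × 0.74 / 0.915 + 0.34) = 0.93, an interval 7% narrower;
- diabetic mean 7.0: 4% narrower; diabetic mean 9.0: 25% narrower.

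Table 1's 10% target also shrinks, because the mean without diabetes is about 4.4 to 4.6: by 6%, 5% and 9% in the same three cases. At the low end the two cancel. The calculation further treats endline spread like baseline spread. Under the normal model with correlation r between baseline and endline FBG, the lost numbers are repaid only if 1 − 0.26r² is below 0.915, that is r above about 0.57.

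**6. Finding the known cases.** Swahili Qn104 asks about 12 months again, so it adds nothing after Swahili Qn103. The parallel Swahili hypertension item, Qn100, does ask *ever*. Both point to a translation slip. A treated person with FBG at or below 7.0 who has not yet taken that day's drug meets neither part of the section 2.6.1 definition as Qn122 captures it. If the diagnosis is older than a year, Swahili Qn103 misses it too.

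**The case against.** **The target population is a choice.** The general objective and hypothesis 1 concern street-food consumers, not consumers free of diabetes, and Objective 1 needs people with diabetes enrolled. This stands. A reader might infer that their eligibility is an error, or that the restricted analysis must replace the main one. The documents support neither: the all-participant comparison answers the stated objective.

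**An analysis subset is commonly left to the SAP.** Partly stands, so its absence is not called an omission here. The eligibility rule, the Table 4 outcomes and covariates, and the questionnaire wording are fixed in the protocol.

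**FBG is not a named primary outcome, and N was set on waist-hip ratio.** This stands and limits the weight of the point. FBG is still a main target indicator and a modelled outcome.

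**Baseline adjustment would absorb stable differences.** True if the GLMM uses each person's baseline value. It does not help the planned t-test, nor remove changes due to treatment.

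**Hypertension is referred too, and blood pressure is a named primary outcome.** The treatment argument does carry over and is not sized here. The other half does not: raised blood pressure is a risk factor for diabetes, whereas diabetic FBG is the disease itself.

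**The section 2.6.1 definition does not use Qn103.** Correct. The mistranslation matters for recognising known cases that the glucose reading and a same-day medication question miss.

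**Conclusion.** The point holds as a matter of precision and interpretability in the FBG analyses, plus one clear translation error. About 25 people per arm supply roughly 30% of the planned FBG variance, with a range of 19% to 69%. This rests on the national 9.1% applying to these consumers and, for the range, on diabetic means that the documents do not give.

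Three stronger readings are tempting and are not supported:

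- That this group supplies most of the variance: this needs a diabetic mean near the top of the assumed range.
- That referral biases the comparison: it applies in both arms, and bias needs a difference in uptake or prevalence. With three markets per arm that is possible, but nothing in the protocol predicts it. A 20-point uptake gap would move the difference by only 0.02 to 0.05 mmol/L.
- That leaving these people out surely narrows the interval by more than the lost numbers widen it: the gain depends on clustering, on the correlation between baseline and endline, and on the smaller target.

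The case is firmest for Table 4, where pooling makes the FBG model hard to interpret, and for Qn103, which departs from its own English source.

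**What to change.** 1. Before baseline data collection, correct Swahili Qn103 to ask *ever*, matching the English item and Swahili Qn100.
2. Keep all participants for Objective 1 and for the all-participant FBG comparison between arms. In section 2.6.4, pre-specify beside it an FBG comparison in participants without diabetes at baseline (section 2.6.1 definition plus any known diagnosis), adjusted for baseline FBG. Status is measured before the intervention, so this does not select on a post-randomisation event.
3. State that the Table 4 FBG model is fitted in participants without diabetes at baseline, and whether the others remain for the other components of the joint model.

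Eligibility and referral stay as they are. The cost is one translated line, a few sentences in section 2.6.4 and Table 4, and about 9% fewer people in the restricted analyses. The protocol should not promise a precision gain in return.
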